### Ethical Considerations

All procedures will be conducted in accordance with the Declaration of Helsinki. Written informed consent will be obtained, and participants will be free to withdraw from the study at any time. Patient data will be stored in a secure and structured database requiring access authorization via key card. The study data from the questionnaires will be collected via Qualtrics, a secure, web-based software platform designed to facilitate data collection and management for research purposes. Data are available from the corresponding author after agreement of the ethics committee. All procedures will be conducted under continuous supervision by trained personnel, with safety monitoring implemented throughout NGF-induced pain and neurophysiological testing. Participants will undergo comprehensive screening prior to inclusion, including TMS-specific safety questionnaires and exclusion of individuals with contraindications (eg, neurological, psychiatric, or implanted electronic or metal devices). During experimental sessions, participants will be closely monitored for adverse events (eg, excessive pain, dizziness, anxiety, and skin irritation), and all procedures (TMS, EMG, EEG stimulation, pressure, and thermal testing) can be immediately paused or terminated upon request. NGF injections (GMP grade), which have been documented as safe in humans [124-126], will be administered using sterile techniques, and expected transient muscle soreness will be monitored during visits; participants will be instructed to report any unexpected or prolonged symptoms. Standardized adverse event reporting procedures will be followed, including documentation, clinical assessment, and, if necessary, referral for medical evaluation.

## Results

### Overview

All study procedures have been approved by the Western University Health Science Research Ethics Board (review reference 2025-125757-103291). Funding was provided by the Canadian Institutes of Health Research under grant number 517,783 for the period 2024‐2029. Recruitment for the study began in April 2025, and all data collection is expected to be completed by 2028. As of April 2026, we have enrolled 26 participants. To date, 4 participants have been excluded: 1 due to a lack of pain, 1 due to a poor-quality EEG signal, and 2 due to the impossibility of obtaining TMS hot spot. Results are expected to be published at the end of 2028. Data will be made available on request. The results will be disseminated through peer-reviewed publications and presentations at national and international conferences.

### Data Quality Control and Handling of Missing Data

Participants who do not develop NGF-induced pain (PRTEE=0 on days +2 and +4) will be excluded. Data quality criteria will be applied across modalities, including successful elicitation of MEPs for ≥90% of TMS pulses and ≥90% marker tracking for motion capture. EEG analyses will be restricted to high-quality, artifact-free data: segments contaminated by eye movements, muscle activity, or excessive amplitudes (±75‐100 µV) will be rejected using automated or visual procedures. For resting-state analyses, PAF will be estimated only when at least approximately 3 minutes of clean data are available and a clear, stable alpha peak (8‐12 Hz) is identifiable; datasets with excessive channel noise (>10% bad channels), insufficient data, or unstable spectra will be excluded. For somatosensory-evoked potentials, trials with artifacts will be discarded, and analyses will require ≥80% of clean trials; averaged waveforms must show identifiable and temporally consistent components (eg, N20 and P25); otherwise, they will be excluded [127-129]. Missing data across visits and modalities will be handled using full information maximum likelihood within growth curve models under a missing-at-random assumption, and all exclusions and missing data patterns will be reported.

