Here, we outline the experimental protocol and statistical analysis plan to examine individual differences in motor behavior (multidimensional movement task and muscular synergies), cortical mechanisms (corticomotor excitability, peak alpha frequency (PAF), and intracortical inhibition and facilitation), sensorimotor integration (sensory-evoked potentials [SEPs]), cognitive function (multisource interference task [MSIT] and questionnaires), and pain modulation (conditioned pain modulation [CPM]) in response to the progressive development, persistence, and resolution of clinically relevant elbow pain (intramuscular injection of nerve growth factor [NGF] into the extensor carpi radialis brevis [ECRB] muscle). We hypothesize that individuals with low sensorimotor cortex excitability, higher intracortical inhibition, reduced sensorimotor integration, central sensitization, and a passive cognitive response strategy will have less variable motor behaviors and more severe, longer-lasting pain.

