### Sample Size

The trial is conservatively powered based on the use of separate multiple regression models to determine which mechanistic variables predict motor outcome at each time point. This calculation is based on 20 mechanistic variables: sensorimotor cortex excitability × 4 (map, SEPs, SICI, and ICF), sensorimotor integration × 1 (PAF-EEG), pain modulation × 2 (HPTs and PPTs), cognitive response × 4 (MSIT-easy-hard × 2 conditions), and physical activity or cognitive response × 6 (MPQ-SF, TSK-13, CSQ-R, PRTEE, LMSS, and PBQ), plus 3 a priori selected interactions and demographic variables × 3 (age, sex, and gender). We require 150 participants to achieve a power of 80% with a 5% significance level to detect a medium effect size and allowing for 10% loss to follow-up (based on our prior studies). The significance level was adjusted for multiple testing using a Bonferroni correction with an assumed correlation between predictors of 0.1. Using an alternative approach of 5‐10 participants per parameter, a sample of 150 could accommodate 15-30 parameters.

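### Whole participants have been dropped for one failed modality, against the article's own missing-data rule; the no-pain exclusion is applied after injection; and the 150 carries no allowance for exclusions

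*Protocol article*

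**What the plan says.** The protocol article's section on Data Quality Control and Handling of Missing Data works at two levels. One rule removes people: "Participants who do not develop NGF-induced pain (PRTEE=0 on days +2 and +4) will be excluded". The remaining rules concern measurements (EEG datasets, evoked-potential trials, MEP and marker-tracking yield). For what is then missing, the section states: "Missing data across visits and modalities will be handled using full information maximum likelihood within growth curve models". Missingness is assumed to be at random. The section also commits to reporting every exclusion. Statistical Analysis gives the use of all available data as one reason for choosing growth curve models.

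The Results overview gives 26 enrolled by April 2026 and reports "4 participants have been excluded: 1 due to a lack of pain, 1 due to a poor-quality EEG signal, and 2 due to the impossibility"; the last two are the cases in which no TMS hot spot could be found.

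The Introduction predicts that people with low sensorimotor cortex excitability, among other features, will show "less variable motor behaviors and more severe, longer-lasting pain". The primary outcome is motor variability, and Statistical Analysis plans two models, one for kinematic variability and one for muscle synergies. PRTEE appears in Sample Size among the predictors.

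On numbers, Sample Size says "We require 150 participants to achieve a power of 80% with a 5% significance level to detect a medium effect size". The only margin it states is in the words "allowing for 10% loss to follow-up (based on our prior studies". It makes no provision for exclusions and does not say whether excluded participants are replaced.

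**The concern.** Three things do not fit together.

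- **Conduct against plan.** If a missing modality is to be handled by likelihood, a poor EEG recording or an absent hot spot should cost that modality and not the participant. Removing the person also discards kinematic and EMG data, which do not depend on EEG or TMS.
- **Who is removed.** Failure to find a hot spot could mark low corticomotor excitability, and low excitability is the group about which the hypothesis makes its prediction. The no-pain rule cuts off the bottom of the pain distribution using information available only after the first injection.
- **Numbers.** Exclusions reduce the evaluable sample on top of loss to follow-up, and only the latter was budgeted.

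At stake are representativeness in the variables the study is about, and power. If remaining visits are not collected for excluded participants, their data cannot be recovered at analysis.

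**Working it through.** **1. Texts side by side.**

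| Place | Unit affected | Consequence |
|---|---|---|
| Data Quality Control: EEG, evoked-potential, MEP and marker criteria | trial or dataset | that measurement is missing, handled by likelihood |
| Data Quality Control: PRTEE=0 on days +2 and +4 | participant | removed |
| Statistical Analysis | participant-visit | all available data used |
| Results overview: 1 EEG, 2 hot spot | participant | removed |

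The last row conflicts with the first and third. The no-pain case follows its own stated rule, so it is a matter of design choice and not of inconsistency.

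**2. The plan's own figure.** 150 × 0.9 = 135 evaluable. The article gives no number for a medium effect and no sidedness. One set of assumptions returns 150 exactly: r = 0.3; 20 variables; α = 1 − 0.95^(1/20^0.9) = 0.00345 (a Bonferroni-type level adjusted for a correlation of 0.1); one-sided; 80% power. Then n = ((z₁₋α + z₀.₈)/atanh 0.3)² + 3, rounded up to 135, and 135/0.9 = 150. Other readings give other totals: two-sided with r = 0.3 gives 152, or 169 after inflation. What matters here is that the whole 10% is used on follow-up loss.

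**3. Exclusions so far** (exact 95% intervals).

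- All four among the 26: 4/26 = 15.4% (4.4% to 34.9%). If the true rate were 10%, four or more of 26 would occur with probability 0.26.
- Four in addition to the 26: 4/30 = 13.3% (3.8% to 30.7%).
- Hot-spot cases counted as screen failures: 2/26 = 7.7% (0.9% to 25.1%). Taking them out of the denominator as well gives 2/24 = 8.3%.
- No-pain case alone: 1/26 = 3.8% (0.1% to 19.6%).

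**4. Projection without replacement.** Retained = 150 × (1 − e). After follow-up loss = that × 0.9. Enrolment needed for 135 after both = 135/0.9/(1 − e) = 150/(1 − e), rounded up.

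| Exclusion rate e | Retained of 150 | After a further 10% loss | Enrolment for 135 after both |
|---|---|---|---|
| 4/26 | 127 | 114 | 178 |
| 4/30 | 130 | 117 | 174 |
| 2/26 | 138 | 125 | 163 |
| 1/26 | 144 | 130 | 156 |

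**5. What the no-pain rule does to the planned models.** Assume a mechanism, pain and motor variability are jointly normal with all pairwise correlations 0.30, and the lowest fraction on pain is dropped. The variance of pain falls to v = 0.839 for 1/26 dropped and 0.712 for 10% dropped.

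- Pain on mechanism: 0.30v/(1 − 0.09(1 − v)) = 0.255 and 0.219, down 15% and 27% from 0.30.
- Motor on mechanism, unadjusted: (0.30 − 0.09(1 − v))/(1 − 0.09(1 − v)) = 0.29 and 0.28, down about 4% and 6%.
- Motor on mechanism, adjusted for pain: (0.30 − 0.09)/(1 − 0.09) = 0.23, unchanged, because selection is then on a variable in the model.

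**The case against.** **The no-pain rule has a design reason.** The study is about responses to pain as it develops and resolves, and the fourth visit is timed from resolution. Someone with PRTEE=0 on both days has no resolution date, so that visit is undefined for them. The criterion is explicit and narrow, and exclusions will be reported. This stands: restricting the primary analysis to successful inductions is defensible, and including non-responders in the primary set is debatable.

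**Selection on the outcome.** A reader might infer that the rules select on the primary outcome and bias its coefficients by 15% to 27%. The documents do not support that. No rule selects on motor variability, those percentages belong to a model with pain as outcome that Statistical Analysis does not plan, and step 5 shows little or no shift in the planned models. What remains is that pain severity is truncated, both as a hypothesised consequence and as a predictor.

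**Timing.** A reader might also infer that all four were removed after baseline. That is shown only for the no-pain case. Mapping intensity depends on a day 0 motor threshold, which requires a hot spot, so those two may have failed before any injection. They would then be screen failures, possibly with no later motor data to keep.

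**The 10% allowance.** A reader might infer that it is already exceeded. It covers loss to follow-up and not exclusions, and the observed rate is compatible with 10%. It is below 10% if the hot-spot cases are screen failures.

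**Missing predictors.** It is tempting to add that a large share of visits will drop out for lack of one predictor. That needs an assumed missingness per modality and listwise deletion, and the article proposes neither. Likelihood can cover predictors if they are modelled jointly, and the implementation belongs in the analysis plan.

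**Conclusion.** The point holds in three limited parts.

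1. **Contradiction.** Whole-participant exclusion for one failed modality, reported for three people, does not agree with the article's rules on data missing across modalities and on using all available data. This rests on the text alone. That hot-spot failure marks low excitability is plausible but not shown. If it does, the missing TMS values may depend on the unobserved excitability, which would strain the missing-at-random assumption.
2. **Post-injection selection.** The PRTEE=0 rule truncates pain severity. Its effect on the planned motor models is probably small at the rate seen so far (1/26), under the assumed correlations of 0.30. It matters more for any statement about who develops more severe or longer pain.
3. **No allowance for exclusions.** At the current rate and without replacement, about 127 of 150 would remain before follow-up loss, or 138 on the screen-failure reading. With the 10% loss the plan expects, these become about 114 and 125, both below 135. The interval on 4/26 is wide, so this is a warning about planning and not a demonstrated shortfall.

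**What to change.** - Reconcile the Results overview with Statistical Analysis and Data Quality Control. Keep every injected participant with motor data in both growth curve models, set the failed modality to missing, and state that predictors are modelled jointly or imputed. Note that missing TMS values may not be missing at random. Retaining these participants helps the motor trajectories and the other coefficients more than the TMS coefficients.
- Classify failures found before the first injection as screen failures, and report the timing of the three modality exclusions.
- Add a sensitivity analysis of all injected participants, including those with PRTEE=0, using the visits they have, since the fourth visit is undefined for them.
- State whether excluded participants are replaced. If not, restate the expected evaluable number. With only the no-pain rule in force at 1/26, keeping 135 after 10% follow-up loss would need about 156 enrolled.

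The cost is plan wording and extra analysis work, and the average pain effect in the sensitivity analysis will be slightly diluted by non-responders. With 26 enrolled, the change is still cheap.

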##### Mapping

TMS mapping will be used to identify the motor cortical representation of the ECRB and assess corticomotor excitability, following a rapid and reliable procedure [58]. Rapid mapping will be performed over a 70 mm × 70 mm area flat grid within a neuronavigation display. The grid will be centered on the hotspot, extended +3.5 cm and −3.5 cm in the frontal (mediolateral) plane and +3.5 cm and −3.5 cm in the sagittal (anteroposterior) plane, and curved and superimposed on a scaled generic brain image and localized relative to Cz. The pseudorandom walk method will involve delivering 120 stimuli at 120% of day 0 rMT at randomized locations within the grid, with a minimum of 4-second interstimulus interval, ensuring an average density of 4 stimuli per cm² to achieve a dense distribution of stimulation sites for accurate interpolation and peak identification [59-61]. The neuronavigation display will be monitored to confirm even stimulus distribution and prevent consecutive stimulations from being too close [62].

Motor maps will be generated offline using a custom Python script (scipy.interpolate.griddata) with a triangular linear interpolation used to create a continuous surface map from 3D MNI stimulation coordinates and corresponding peak-to-peak MEP amplitudes, while trials with background EMG activity will be excluded. The resultant motor map will be divided into 2500 partitions, each assigned an interpolated MEP value based on the nearest acquired data. Map volume will be calculated following van de Ruit et al [62], although a 50-μV minimum threshold will be used instead of the “greater than 10% of the maximum MEP” threshold, to include more responses and minimize outlier influence [58].

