##### Paired Pulse

Paired pulse TMS will be performed to assess the short-interval intracortical inhibition (SICI) and the intracortical facilitation (ICF) for the right ECRB muscle following a standardized protocol [63]. Each condition will be tested in 12 trials at interstimulus intervals of 2 ms for SICI and 13 ms for ICF. As previous studies have shown that muscle pain reduces MEP amplitude [11,64] and that the size of the test response influences SICI magnitude [65], a 0.3-0.4-mV test response will be selected to maintain consistency across visits, even if corticomotor excitability decreases due to pain. The conditioning stimulus will be set at 90% rMT. An additional 12 unconditioned test trials will be recorded, totaling 36 trials, which will be presented in pseudorandom order. MEP responses will be measured as peak-to-peak amplitudes, and conditioned responses will be expressed as a proportion of the unconditioned test response.

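### Requiring an MEP on at least 90% of TMS pulses, read as written, conflicts with the mapping and SICI designs and discards TMS data because of the value being measured

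*Protocol article*

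**What the plan says.** Under Data Quality Control and Handling of Missing Data the article states: "Data quality criteria will be applied across modalities". For TMS the criterion is "successful elicitation of MEPs for ≥90% of TMS pulses". No pulse type is exempted. The clause names no unit (trial, block, visit or participant) and no consequence of failing. The same paragraph handles missing data by full-information maximum likelihood, assuming missingness at random.

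The pulses are described elsewhere:

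- **Mapping:** "Rapid mapping will be performed over a 70 mm × 70 mm area flat grid", centred on the hotspot, with "delivering 120 stimuli at 120% of day 0 rMT at randomized locations within the grid". Operators monitor that the pulses are evenly spread. Map volume counts responses above a 50 µV floor.
- **Paired Pulse:** 12 SICI, 12 ICF and 12 unconditioned trials, 36 in all, where "a 0.3-0.4-mV test response will be selected to maintain consistency across visits".
- **TMS Overview:** a response counts as an MEP at 50 µV or more, and resting motor threshold is the intensity that gives one on at least half of trials.

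The Introduction expects "individuals with low sensorimotor cortex excitability, higher intracortical inhibition" to go with less variable movement and worse pain. The Discussion ties this to reduced map volume and increased SICI.

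**The concern.** In mapping, a site with no response is a result: it shows where the muscle's representation ends. In SICI, a suppressed response is the effect being measured. A rule that treats absent MEPs as poor quality therefore rejects valid observations.

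The chance of rejection depends on the quantity measured. Small maps and strong inhibition fail more often, and these are the hypothesised predictors. For mapping, painful visits are also more exposed: intensity is fixed at 120% of the day 0 threshold, while the Paired Pulse section expects muscle pain to reduce MEP amplitude. Missingness that depends on the unobserved value is not missing at random in general, so the stated likelihood method does not repair it. At stake are the TMS predictor data, their range, and the power to relate them to motor variability.

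**Working it through.** **1. The article's own mapping figure.** Mapping claims "ensuring an average density of 4 stimuli per cm²". The grid is 7 × 7 = 49 cm², and 120/49 = 2.45 per cm², so the figure does not reproduce. A density of 4 per cm² needs 4 × 49 = 196 pulses on this grid; 120 pulses at that density cover 30 cm². The statements need reconciling, but the result below does not depend on it: if the pulses really fell on 30 cm², 90% of that (27 cm²) would have to respond, so the map's border would again be hardly captured.

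**2. Mapping threshold.** 0.90 × 120 = 108 MEPs. With evenly spread pulses the responding share is about A/49, where A is the responsive area, so the rule needs A ≈ 0.90 × 49 = 44.1 cm². The largest circle that fits in the grid has area π × 3.5² = 38.5 cm², or 78.5%.

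**3. Chance that a map passes.** P(X ≥ 108), X ~ Binomial(120, A/49). A is an assumption.

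| A (cm²) | Share | Expected MEPs | P(pass) |
|---|---|---|---|
| 30 | 61% | 73.5 | about 1e-12 |
| 38.5 | 79% | 94.3 | 0.0008 |
| 40 | 82% | 98.0 | 0.009 |
| 42 | 86% | 102.9 | 0.11 |
| 44.1 | 90% | 108.0 | 0.58 |
| 46 | 94% | 112.7 | 0.97 |

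Pooling mapping and paired-pulse trials does not rescue it. 0.90 × 156 = 140.4, so 141 are needed. If all 36 paired-pulse trials respond, 141 − 36 = 105 map responses remain necessary, or 105/120 × 49 = 42.9 cm².

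**4. Paired-pulse threshold.** 0.90 × 36 = 32.4, so 33 of 36 must respond and at most 3 may fail. A 50 µV cut against a 0.3–0.4 mV test response is a conditioned/test ratio of 50/300 = 0.167 to 50/400 = 0.125.

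**5. Chance that a paired-pulse block fails.** Assumptions: lognormal amplitudes, mean equal to test size × ratio, trial CV 40–100%, ICF ratio 1.3. For each trial type p = P(amplitude ≥ 50 µV). The three binomials of 12 are summed, and the block fails below 33.

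| Test size, CV | SICI ratio 0.2 | 0.3 | 0.4 |
|---|---|---|---|
| 0.4 mV, 40% | 10% | 0% | 0% |
| 0.4 mV, 60% | 46% | 2% | 0.1% |
| 0.3 mV, 60% | 91% | 26% | 2% |
| 0.3 mV, 100% | 99% | 84% | 57% |

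Failure rises with inhibition in every row. If the 12 SICI trials are judged alone, 0.90 × 12 = 10.8, so 11 must respond; at ratio 0.2 and CV 60% failure is then 90% (0.4 mV) to over 99% (0.3 mV).

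**6. What truncation does to an association.** Take a linear model with slope 0.30, residual SD 1 and a standard normal predictor: the correlation is 0.30/√1.09 = 0.29. Dropping predictor values below −0.5 SD leaves the slope at 0.30 but cuts the predictor SD to about 0.70 (variance 0.49). The correlation becomes 0.30 × 0.70/√(1 + 0.09 × 0.49) ≈ 0.21. Range and power are lost; the slope need not be biased.

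**The case against.** The best defence is that the sentence is loose wording meant for hotspot or test pulses. Taken literally it would also catch the threshold-finding pulses, which by definition give an MEP only about half the time. A condensed article may leave the scope of a quality rule to a fuller document. The Results list four exclusions among 26 enrolled (one for lack of pain, one for EEG quality, two with no hotspot) and none under this rule. These points make the narrow intent plausible. They do not remove the conflict, because the article states a rule and its words cover every TMS pulse. The exclusion list counts participants, so it does not show whether maps or visits were discarded, and quality control may be pending.

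Other limits stand. TMS measures are secondary outcomes, and measurement of the primary motor outcomes does not depend on this rule. The pain-visit argument applies to mapping only, since the paired-pulse test response is held constant across visits. The article already drops mapping trials with background EMG and promises to report all exclusions.

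A reader might infer four stronger conclusions that the article does not support:

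- **That the rule can never be met.** Responsive area is not given, and a map of 46 cm² would usually pass.
- **That it removes low-excitability and high-inhibition participants.** No unit or consequence is stated.
- **That map loss is mainly selective.** If most maps fail, the loss is near total; selection applies chiefly to SICI and to maps near the cut-off.
- **That associations are biased toward the null.** Selection on a predictor need not bias its slope. Likelihood methods that model the predictor could be biased when missingness is not at random, but neither size nor direction has been shown.

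**Conclusion.** The point holds as a conflict between a stated rule and the measurements it governs. Any map whose border lies well inside the grid fails: the pass probability is below 0.001 up to about 38 cm². This rests on an assumed responsive area and on even, independent placement of pulses. Paired-pulse blocks fail more often with stronger inhibition. The direction is the same in every scenario, but the size is not: 10–99% at a ratio of 0.2 and 0–57% at 0.4, over test responses of 0.3–0.4 mV, CV 40–100% and an ICF ratio of 1.3. The article gives neither CV nor ratio.

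Applied literally, the sure costs are lost TMS predictor data and lost range and power, through a mechanism that the missing-at-random assumption does not cover. Whether participants are lost, and which way any estimate would move, is not established. This should be fixed, but because the measures are secondary it is not a defect that blocks the trial.

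**What to change.** Reword the TMS clause in the quality-control section to say which pulses it covers, what unit is judged and what follows a failure.

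- **Unconditioned test pulses (12 per visit):** keep the MEP-elicitation criterion here only. At 90%, 11 of 12 must respond. Under the assumptions above this fails in at most about 9% of blocks (0.3 mV, CV 100%) and almost never at CV 60% or less.
- **Mapping and conditioned pulses:** use criteria independent of MEP size, for example at least 90% of pulses at the intended coil position and free of background EMG. Keep responses under 50 µV as valid data.

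The stimulus density should be reconciled with the pulse count and grid size in the same edit.

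The cost is one reworded sentence and a recheck of any TMS session already flagged. No new data are needed, and with 26 of 150 enrolled the change can be made before most data are screened.
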